**8. Statistical analyses**

Study analyses will consider study **feasibility** as well as **clinical** (statistical) outcomes. Means and standard deviations (for continuous variables) and frequencies and proportions (for categorical variables) will be used to summarize case mix and outcome variables for groups. Qualitative comparison of variable balance will be made, including determination of prognostic importance.^68^ Descriptive statistics of training time and number of training sessions for the treatment group (collected via tablet usage data) will be used to evaluate dose-response and adherence.

**8.1 Feasibility Outcomes**

Specific feasibility objectives have been identified related to study process, resources, management, and treatment assessment.^69^ These objectives are listed below and a detailed description of each outcome and measurement variables is provided in Appendix D. Aside from the treatment outcomes that undergo statistical analysis, feasibility outcomes will be treated as binary, with “success” indicating the protocol is sufficiently robust to move forwards with the large RCT with only small or
[figure not shown]
no adaptation required, and “revise” indicating a need for more substantive change before proceeding. The number and extend of objectives requiring revision will determine whether the feasibility study data can be conflated with those produced in the larger subsequent RCT.

**8.2 Clinical Outcomes**

***8.2.1 Primary analysis:*** Post-treatment WST skill *capacity* scores will be compared in the experimental and control groups using analysis of covariance (ANCOVA), controlling for baseline score as a covariate.^70^ Borm et al.^71^ demonstrate that correlation between pre- and post-intervention scores (ρ) influences analysis power; when ρ > 0.5, change score is more powerful than direct post-intervention comparison. However, when ρ lies between 0.2 and 0.8, ANCOVA (controlling for baseline score) further reduces the required sample size by 10-40% over change score. Given that preliminary data suggest ρ ~ 0.5,^72^ ANCOVA should provide the most powerful analysis, in addition to reducing error variance and allowing modification when statistical assumptions are not met.^73^ Unequal cell sizes will be accommodated using Method 1 adjustment^74^ and diagnostic assessments made for model assumptions. Significance testing (*p*) and marginal means with 95% confidence intervals will be estimated. Effect size (partial η^2^) will be calculated as a ratio of the effect and total sums of squares, with a 95% confidence interval . To preserve prognostic balance, primary analysis will be based on intention-to-treat; however, since one objective is to estimate the treatment effect, secondary analysis on a per-protocol basis (subjects who adhere to treatment) will also be conducted for comparison.^75^

***8.2.2 Secondary analysis:*** ANCOVA will be used to compare post-treatment scores between the experimental and control groups for WST skill **safety** scores as well as for wheelchair **confidence** (WheelCon) scores and **mobility** (LSA). In each case, baseline score will be used as a covariate. Subjects’ **satisfaction with performance** of meaningful activities (WhOM score) will be analyzed using analysis of variance (ANOVA). Mean administration time for the HUI will be calculated and a preliminary evaluation of change in the treatment group (paired sample *t-test*) will be conducted.

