**Methods**

**
[figure not shown]
1. Research Design.** This 2-year feasibility study will use a two-site (Winnipeg and Vancouver) randomized controlled trial to compare differences in older adults’ wheelchair mobility skills with EPIC WheelS versus usual care. Subjects will be randomly assigned to the experimental group (usual care + EPIC WheelS) or a control group (usual care only) using a 1:1 allocation ratio between groups. To support balance between groups and masking of assignment, a central computerized randomization process will be designed by our team statistician ([name]), with an undisclosed block size and stratified by site (Winnipeg *n* = 20; Vancouver *n* = 20). Once subjects are enrolled, the Study Tester will collect baseline data and enter them into a secure database. The Site Coordinator will contact [name] via telephone or email and obtain group assignment within 48 hours. Subject contact information will be forwarded to the appropriate group Trainer to arrange for an initial training session or social visit. To address bias, subjects will be instructed not to discuss their program and Study Testers will be blinded to group allocation.

Experimental group subjects will attend 2 training sessions with an expert Trainer. The Trainer will individualize a structured home training program, delivered via a computer tablet, and subjects will train for 1 month. The Trainer will make telephone contact at the end of weeks 1 and 3. Control group subjects will receive 2 social visits to address attention balance through exposure to study personnel. In addition, they will be provided with a similar computer tablet with cognitive training games to account for tablet device and activity exposure.

**2. Assessments.** The clinical outcome measures will be collected at baseline (pre-randomization) and post-intervention. A 1-month intervention will provide ≥ 8 hours of training, which is comparable to clinical studies using the WSTP where a significant improvement in skill capacity was observed.^17-19^

**3. Subjects.** A total of 40 community-dwelling MWC users living in Winnipeg and Vancouver (20 at each site) will be recruited on a volunteer basis (see Section 8.1 for sample size justification). To optimize the impact of the treatment, individuals with less than one year of MWC use will be recruited as they are still developing routines and patterns of wheelchair use and potentially more amenable to adapting their mobility techniques.^12^

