**8.4 Sample size justification*.*** To address the feasibility outcomes, the number of subjects is large enough to represent the target population and assess the feasibility criteria.^69^ In addition, the sample size is powered to detect a statistically significant difference between groups and provide a reasonable estimate of a treatment effect. The sample size calculations are based on the primary *clinical* outcome (WST), as this will be used in subsequent EPIC WheelS studies. Research in the field of wheelchair skills training is still maturing, with 3 published studies using actual users, and given the novel home program approach an ∝ of .10 was selected to ensure a potentially beneficial treatment effect does not go undetected (Type I error rate). To minimize the risk of identifying such an effect merely by chance (Type II error), the study is powered at 90%. Based on a sample size calculation formula for ANCOVA in RCT designs^71, 83^ each group would require 15 subjects (see Appendix Q for details). In previous Canadian trials, a 9-18% dropout rate has been reported; conservatively adjusting for a 25% dropout rate, a total study N of 40 is planned (n = 20 for each group).

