The two sites selected for the study are Winnipeg and Vancouver. These two locations represent different provincial approaches to wheelchair procurement in Canada and therefore enable us to assess whether disparate approaches to health services will contribute to complications in running a multi-site trial. Manitoba and British Columbia have substantially different wheelchair funding systems, as well as geographic, cultural and climate differences. Both sites have large populations of older adult MWC users, with representatives from both sites previously contributing to the development of the EPIC WheelS program and committed to ongoing input including knowledge translation activities. The study will be conducted at the Blusson ICORD Pavilion and Rehab Research Lab (GF Strong Rehab Hospital) in Vancouver both locations have private rooms for data collection and a separate 600 square foot space housing the WST equipment. The Health Sciences Rehabilitation Centre in Winnipeg is the primary tertiary care centre for the province and has dedicated space for wheelchair training and testing, including the WST equipment.

**2. Recruitment**. There is a substantial and growing pool of older adult MWC users to draw from. The Manitoba Wheelchair Program (MWP), a publicly funded long-term loan program and primary provincial wheelchair provider, identifies nearly ***7200 MWC users over 55*** ***years*** currently in Manitoba. [name] has established connections with clinicians and provincial agencies that provide wheelchair prescription and procurement. British Columbia has a population roughly four times as large and is expected to have at least ***25,000 older adult MWC users***. [name] has developed relationships with therapists who prescribe wheelchairs in the Lower Mainland of Vancouver. For this feasibility trial, we expect to draw on a broad pool of potential subjects through our established relationships with community-based therapists; advocacy and consumer-based groups; recruitment advertising included with delivery of wheelchairs to new users via the MWP; and public advertisement using print, television, and web-based media.

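### Randomisation is stratified by site, but the primary and secondary models leave site out; if site is prognostic beyond baseline, intervals are too wide and the test is conservative

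*Combined protocol and SAP*

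**What the plan says.** Methods, 1. Research Design, sets up a two-site trial "using a 1:1 allocation ratio between groups", with computerised randomisation "with an undisclosed block size and stratified by site" and 20 subjects planned at each site.

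Section 8.2.1 compares post-treatment WST capacity between groups by "analysis of covariance (ANCOVA), controlling for baseline score as a covariate". Section 8.2.2 uses ANCOVA for WST safety, WheelCon and LSA and adds: "In each case, baseline score will be used as a covariate". Satisfaction on the WhOM "will be analyzed using analysis of variance (ANOVA"), with no covariate or second factor named. HUI3 change is examined within the treatment group by a paired t-test.

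Site appears in none of these models. The adjustment for unequal cell sizes in 8.2.1 names no second factor either.

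The description of the study sites, just before the Recruitment paragraph, says why the two were chosen: "Manitoba and British Columbia have substantially different wheelchair funding systems, as well as geographic, cultural and climate differences".

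**The concern.** Stratified 1:1 allocation balances site between the arms, so a site difference in scores cancels out of the treatment contrast. A model without site does not know this. It leaves the between-site variation in the residual and reports a standard error larger than the true sampling variability of the estimate.

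This trial is meant to supply an effect-size estimate for planning a larger RCT, so interval width matters at least as much as the p-value. Section 8.4 also relaxes alpha so that a useful effect is not missed, and a conservative test partly undoes that choice. Section 8.2.1 defends ANCOVA on grounds of power and reduced error variance, and the same argument applies to site.

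**Working it through.** **Inputs from the documents.** Planned difference 9.3 points and SD 9.5 points (the sample size section, from WST change scores); pre/post correlation about 0.5 (8.2.1); "an ∝ of .10 was selected" and "the study is powered at 90" per cent (8.4); 15 evaluable per group, 25% dropout, N = 40 (8.4). The sidedness of alpha is not stated.

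**Reproducing the plan's sample size.** Two-sided alpha 0.10, power 0.90:

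- Two-sample formula: n = 2 × (1.645 + 1.282)² × 9.5² / 9.3² = 17.87 per group.
- ANCOVA factor: 1 − 0.5² = 0.75, so 17.87 × 0.75 = 13.4. That is 14 per group, or 15 with one extra subject per group.
- Dropout: 15 / (1 − 0.25) = 20 per group, 40 in total.

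This agrees with the plan. A one-sided alpha would give 11 (12 with the extra subject), so two-sided is the reading that fits. Appendix Q, which holds the details, is not in the available text, so the step from 14 to 15 is inferred.

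**What omitting site does.** The baseline-adjusted residual SD is 9.5 × √0.75 = 8.23. Let R² be the share of that variance explained by site. R² is an assumption, because the documents give no site difference in WST. With two equal sites it corresponds to a gap after baseline adjustment of 2 × √R² × 8.23: about 3.7 points at 5%, 5.2 at 10%, 7.4 at 20% and 9.0 at 30%. Total residual variance is held at the planned value. To a first approximation the standard error is too large by a factor 1/√(1 − R²), that is 1.03, 1.05, 1.12 and 1.20.

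**Simulation.** Site-stratified 1:1 allocation, 8,000 trials per setting, two-sided alpha 0.10, each data set fitted without and with site. At 20 per group:

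| Assumed R² | SE without / with site | SE too large by | Type I error without site | Power at 9.3 without / with |
|---|---|---|---|---|
| 0% | 2.61 / 2.61 | 0% | 0.10 | 96.6 / 96.6% |
| 5% | 2.62 / 2.55 | 3% | 0.096 | 96.8 / 97.0% |
| 10% | 2.63 / 2.49 | 6% | 0.080 | 97.1 / 97.8% |
| 20% | 2.63 / 2.35 | 12% | 0.069 | 97.7 / 98.6% |
| 30% | 2.64 / 2.19 | 21% | 0.052 | 98.5 / 99.4% |

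With site included, type I error stays at about 0.10 throughout.

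Where there is less power to spare, omission costs more (power without / with site, R² from 0% to 30%):

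- 14 per group, effect 9.3: 88.4/88.4, 89.3/90.2, 89.3/90.9, 90.7/93.6, 91.1/95.6%.
- 20 per group, half the planned effect (4.65): 53/53, 54/56, 53/57, 53/61, 53/67%.

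**Interval width.** The 95% half-width at 20 per group is t × SE, on 37 degrees of freedom without site and 36 with it. At R² = 10%: 2.026 × 2.63 = 5.3 points against 2.028 × 2.49 = 5.0. At R² = 20%: 5.3 against 2.028 × 2.35 = 4.8. In terms of precision, 40 × (2.49/2.63)² ≈ 36 subjects and 40 × (2.35/2.63)² ≈ 32 subjects, so the report would look like a trial of that size.

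**The case against.** The strongest reply is that the harm is hypothetical. The sites are described as differing in funding, geography, culture and climate, not in WST scores. With no site effect beyond baseline, nothing is lost. Section 4.2.1 also averages two baseline WST administrations and has standardised equipment at both sites, so a lasting difference in skill would show at baseline and be partly absorbed by the covariate. With 32 completers, a 10-point raw gap present at both visits gives a standard error of 3.03 without site against 2.93 with it, and power at 9.3 points of 92% against 93%. All of this stands, and it is why the point is conditional.

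A reader might infer a large loss by supposing a 10-point gap after baseline adjustment. With 32 completers, and that gap added on top of the planned variance, the standard error is 3.47 against 2.93 and power 87% against 92%. But that gap exceeds the whole planned effect of 9.3 points, nothing in the documents supports it, and it takes total variance above the planning SD.

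A reader might also infer that an inflated residual SD would be passed to the next RCT. No section says a residual SD is carried forward. The effect size in 8.2.1 is a ratio of effect to total sums of squares, and computed that way it hardly changes when site is added (0.199 either way at a 5-point gap, 0.170 either way at 10). A conventional partial eta-squared would change, but that is not the formula given.

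What survives is that the analysis does not follow the stratification, and that correcting this costs almost nothing.

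**Conclusion.** The point holds as a conditional one. Site is a stratification factor and is missing from every clinical outcome model. If it is prognostic beyond baseline, the standard error at 20 per group is too large by about 3% to 21% for assumed site shares of 5% to 30%, and by nothing at 0%. The power lost is about 1 percentage point or less at the planned effect with 40 subjects, about 1 to 4.5 points at 14 per group, and about 2 to 13 points for an effect half the planned size (R² 5% to 30% in the last two). The wider interval is the main cost.

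The documents do not support saying that the plan certainly wastes power, or that the result is biased or prone to false positives: any error is conservative. The figures assume SD 9.5, correlation 0.5, two-sided alpha 0.10, equal sites and balanced completers. The R² values are illustrative.

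**What to change.** In 8.2.1, add site (Winnipeg/Vancouver) as a fixed effect to the primary ANCOVA alongside treatment and baseline score. In 8.2.2, do the same in the ANCOVAs for WST safety, WheelCon and LSA, and add site as a factor in the WhOM ANOVA. Leave the HUI3 paired t-test as it is: it is a within-group comparison with no treatment contrast to adjust. Whether the WhOM analysis should also adjust for baseline is a separate question.

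The cost is a change of wording and one degree of freedom per model. N and the stated power need not change, and if site has no effect the standard error is essentially the same (2.61 either way at 20 per group). Writing the term in now also removes a choice of model after the data are seen.

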**OVERVIEW**

Many older adults rely on a manual wheelchair for community mobility, but are not provided with the *skills* for independent and effective use of their wheelchair. Suboptimal use of the wheelchair results in substantial social costs such as reduced engagement in meaningful activity, social isolation, and higher caregiver burden. This is a poor use of financial resources, including the cost of wheelchair acquisition and requirements for attendant care. Access to *skills training* is constrained by the expense and limited availability of skilled therapists; demands of patient and/or clinician travel; and lack of training programs designed specifically for older adults. ***E****nhancing* ***P****articipation* ***I****n the* ***C****ommunity by improving* ***Wheel****chair* ***S****kills* (EPIC WheelS) is an individualized home-training program that optimizes learning for older adults while limiting the time demands of expert trainers. Using an affordable mainstream computer tablet device, EPIC WheelS provides a structured training program that can be customized for specific users needs. The tablet is mobile, for in-chair or tabletop use, in home and community locations. A touch screen operated audio-visual display features interactive training and practice activities as well as video-recording capability. Wireless Internet enables user-trainer communication and remote program monitoring and updating by the trainer. A monitored home program that is effective and efficient for older adults has the potential for application to other target groups, particularly those in rural and remote locations with limited access to rehabilitation.

**PURPOSE:** Our purpose is to *evaluate the feasibility and effect size estimate* of a 1-month customized home training program (EPIC WheelS) for improving wheelchair mobility skills among novice older adult manual wheelchair users compared to usual care.

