Despite the pervasive use of wheelchairs as an intervention in rehabilitation, the evidence for training in effective wheelchair use is still underdeveloped. *Structured* *training* has demonstrated excellent potential, but the most effective and efficient means of providing that training remains unclear. Larger multi-site clinical trials are required to establish evidence to inform and direct clinical practice. We propose that this 2-year feasibility trial is not only **critical, but also prudent, prior to moving forward** with an expensive large multi-site randomized controlled trial (RCT). Specifically the results of this study will address 1) **feasibility outcomes** (i.e., recruitment and retention; trainer and subject burden; safety; intervention administration and adherence; perceived benefit) and 2) **clinical outcomes** (i.e., effect size calculations for the primary and secondary measures). Although the principal intent is feasibility, our sample size calculation is based on the primary clinical outcome to provide a reasonable estimate of an effect size for planning the subsequent large scale RCT.

**HYPOTHESES:** We expect that the **feasibility outcomes will be sufficiently robust to support conducting a subsequent multi-site RCT.** We also expect the EPIC WheelS training program will have **a significant treatment effect** with improvement in wheelchair mobility, compared to a control group**.** The primary **clinical** endpoint will be wheelchair skill *capacity*, as measured by the Wheelchair Skills Test (WST). Secondary clinical outcomes will include wheelchair skill *safety*; confidence with wheelchair use; mobility; and user evaluation of performance in participation-oriented activities.

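### Section 8.2.1 does not name the baseline-adjusted group difference in WST points with its interval, and Section 8.2.2 does not specify the effect sizes promised for secondary measures

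*Combined protocol and SAP*

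**What the plan says.** Section 8.2.1 compares post-treatment WST capacity between groups by ANCOVA, "controlling for baseline score as a covariate". It lists three outputs:

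- a significance test;
- marginal means: "marginal means with 95% confidence intervals will be estimated";
- partial eta-squared, which "will be calculated as a ratio of the effect and total sums of squares, with a 95% confidence interval".

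The adjusted difference between the two marginal means, an interval for it, the residual SD and the observed pre-post correlation are not named.

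The Overview gives part of the study's purpose as to "evaluate the feasibility and effect size estimate". It explains that the sample size rests on the clinical outcome "to provide a reasonable estimate of an effect size for planning the subsequent large scale RCT". It describes the clinical outcomes as "effect size calculations for the primary and secondary measures". Feasibility is nevertheless the stated principal intent, and the clinical effects are secondary objectives.

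For the secondary measures, Section 8.2.2 says "ANCOVA will be used to compare post-treatment scores between the experimental and control groups for WST skill" safety, and likewise for WheelCon and LSA. WhOM gets an ANOVA. HUI3 gets administration time and a paired t-test in the treatment group. No effect size or interval is mentioned for any of the five.

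**The concern.** Every yardstick the plan gives for the primary outcome is in WST points. Section 8.4 has the planning difference (9.3), a Smallest Detectable Difference (9.2), and a Minimal Detectable Change (3.0) offered as a proxy for a clinically important difference. Of the planned outputs, only the marginal means are in those points, and their intervals describe the groups, on the natural reading one group at a time. The one between-group measure with an interval, partial eta-squared, has no units and no sign, so it cannot be set against 9.3, 9.2 or 3.0 without conversion.

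At stake is how directly the report answers its own question: how large the benefit is, how precisely it is known, and whether the interval excludes a benefit below the plan's benchmark. For the secondary measures, an effect size promised in the Overview may not be produced. For HUI3, no between-group result is planned at all.

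**Working it through.** **Inputs.** Difference 9.3, SD 9.5, alpha 0.10, power 90%, 15 per group required, 25% dropout, N = 40 (Section 8.4); pre-post correlation about 0.5 (Section 8.2.1). Sidedness is not stated, and Appendix Q, which holds the sizing details, is not in the text reviewed. A two-sided test is assumed.

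**The plan's own figure.** Section 8.4 begins the calculation "Based on a sample size calculation formula for ANCOVA in RCT designs".
- Unadjusted n per group = 2 × (1.645 + 1.282)² × 9.5² / 9.3² = 17.87.
- ANCOVA factor 1 − 0.5² = 0.75, so 17.87 × 0.75 = 13.40. This rounds up to 14, or 15 with a one-subject small-sample correction (inferred).
- 15 / (1 − 0.25) = 20 per group, N = 40. The stated size reproduces.

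**Interval for the adjusted difference.** Residual SD = 9.5 × √0.75 = 8.23. SE = 8.23 × √(2/n), with 2n − 3 degrees of freedom.

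| | 15 per arm | 20 per arm |
|---|---|---|
| 95% half-width | 6.2 | 5.3 |
| 95% interval at 9.3 | 3.1 to 15.5 | 4.0 to 14.6 |
| 90% half-width | 5.1 | 4.4 |
| 90% interval at 9.3 | 4.2 to 14.4 | 4.9 to 13.7 |

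For 15 per arm: SE = 8.23 × √(2/15) = 3.00, and 2.052 × 3.00 = 6.16. The lower 95% limit, 3.1, falls almost on the 3.0-point benchmark, and no listed output shows that directly.

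**Arm intervals are not a substitute.** With 15 per arm, each half-width is 2.052 × 8.23 / √15 = 4.36. The two intervals therefore overlap for any difference below 2 × 4.36 = 8.7 points, although p < 0.10 is reached at 5.1 and p < 0.05 at 6.2. With 20 per arm the corresponding values are 7.5, 4.4 and 5.3.

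**Eta-squared.** At 9.3 points and 15 per arm:
- Effect sum of squares = 7.5 × 9.3² = 648.7.
- Error = 27 × 8.23² = 1,827.6, taking the unrounded residual variance 0.75 × 9.5².
- Covariate = 0.25 × 9.5² × 28 = 631.8.
- Partial eta-squared = 648.7 / (648.7 + 1,827.6) = 0.26, with a 95% interval of about 0.03 to 0.47 by noncentral F. With the residual SD, this converts to roughly 2.8 to 15.6 points.
- The formula written in Section 8.2.1 divides by the total: 648.7 / 3,108.1 = 0.21. That is ordinary, not partial, eta-squared, so the label and the formula give different numbers.

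**Secondary measures, plan against promise.**

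| Measure | Section 8.2.2 | Adjusted between-group difference available? |
|---|---|---|
| WST safety, WheelCon, LSA | ANCOVA with baseline covariate | Yes, from the planned model; not named |
| WhOM | ANOVA, no baseline covariate stated | No |
| HUI3 | Paired t-test, treatment group | No between-group comparison |

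Secondary objective 2 includes the effect of the programme on health-related quality of life. A within-group change cannot estimate that effect.

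**The case against.** The strongest reply is that the information is nearly all there.

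- The difference is one marginal mean minus the other. With equal arms and similar baselines, its half-width is √2 times the arm half-width: 1.414 × 4.36 = 6.17.
- Partial eta-squared is a between-group measure with a planned interval, and the marginal means supply its direction.
- The opening of Section 8 already commits to group means and SDs for the outcome variables. With the residual SD, these imply the correlation.
- It could be argued that the outputs in Section 8.2.1 carry over to the three secondary ANCOVAs.

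Most of this stands, and it rules out stronger readings. A reader might infer that the effect will not be usable, or that the next trial could not be sized. The documents do not support that. A standard partial eta-squared of 0.242, the population value at the planning inputs, gives d² = 4 × 0.242 / 0.758 = 1.28 and n = 2 × (1.645 + 1.282)² / 1.28 = 13.4 per arm, the plan's own figure before rounding. A reader might also infer that overlapping arm intervals will be taken as no effect. The plan proposes no overlap rule and reports p beside the means. Nor is effect estimation the trial's main reason to exist, because feasibility is.

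What remains is that recovery takes extra steps and assumptions: balanced baselines, a residual SD that is not listed, and a choice between two definitions of eta-squared. Any carry-over to the secondary ANCOVAs is not stated, and it could not cover WhOM or HUI3.

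**Conclusion.** The point holds as a reporting gap that can be closed at little cost. The plan names a unitless effect measure and group means, but not the adjusted difference with its interval on the scale it uses for sample size and interpretation. That interval would be about ±6.2 points with 15 per arm and ±5.3 with 20. Separately, the Overview's promise of effect sizes for secondary measures is not carried into Section 8.2.2, most clearly for WhOM and HUI3.

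No test, sample size or feasibility conclusion is affected. The figures assume SD 9.5, correlation 0.5, equal arms and a two-sided test. At correlation 0.5, the residual SD is the same whether 9.5 is the SD of change or of post-treatment scores. Appendices D and Q are not in the text reviewed. If either already specifies the difference and its interval, a cross-reference in Section 8.2 would settle the primary-outcome part.

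**What to change.** **Primary outcome.** In Section 8.2.1, make the baseline-adjusted mean difference (EPIC WheelS minus control) in WST points, with its confidence interval, the headline estimate. Report the ANCOVA residual SD beside it, with the observed correlation between the baseline score (the mean of two administrations under Section 4.2.1) and the post-treatment score. State the interval level, since 95% does not correspond to the alpha of 0.10; a 90% interval would. Keep marginal means and eta-squared as description, and align the eta-squared label with its formula.

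**Secondary outcomes.** In Section 8.2.2, report the same adjusted difference and interval for WST safety, WheelCon and LSA from the planned ANCOVAs. For WhOM and HUI3, add a baseline-adjusted between-group model. The HUI3 result can be labelled preliminary, as the plan already intends.

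**Cost.** This is wording only for the primary outcome and the three secondary ANCOVAs, whose models already produce these outputs. WhOM and HUI3 need a small amount of extra analysis on data already planned for collection at baseline and one month. N stays at 40.
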